##### Process measures

The uptake and implementation of the intervention were monitored in terms of: number of GPs who commence and complete the on-line ALM (described below); number and type of interactions on the discussion forum; and number and content of requests to the diabetes specialist via the on-line request form (described below). GPs who registered for the ALM were also invited to complete on-line surveys at pre-test and post-test regarding self-reported knowledge, attitudes, awareness of need for change (pre-test), intended changes in practice (immediate post-test) or actual changes in practice (follow-up). The surveys consisted of multiple choice, yes-no, and open-ended questions.

##### Intervention group

Systematic reviews identified several CME approaches that were more effective than others. These included: use of multimedia rather than single media; use of multiple educational techniques (*e.g.*, case based learning, discussion groups, personal reflection or audit); more than one exposure to the educational material [18]; and opportunities for practice [27]. GPs in towns allocated to this group were offered an intervention package comprising several features: CME on best practice diabetes care via an on-line ALM, including a moderated discussion forum, self-audit and pre-post ALM reflection exercise, access to specialist advice through an on-line request form, and town-based performance feedback on diabetes monitoring and outcomes. The package was offered via repeated direct mail using evidence-based strategies, including primer postcards, personalised mail, CME or quality improvement (QI) and Continuing Professional Development (CPD) points, reminder gifts (jellybeans and tent calendars with reminder messages), faxed reminders, and an incentive of $200 for ALM completion [28-32]. The content addressed the full range of best-practice care, not solely monitoring metabolic markers, was pilot-tested and drew on the expertise of the Monash Department of General Practice and the Baker IDI Heart and Diabetes Institute. The intervention is to be conducted over two years and designed to not only provide GPs with prerequisite knowledge for optimal primary care management of diabetes, but to provide opportunities to practice and refine skills in the practice setting. The intervention components are:

1. On-line active learning module (ALM): This component of the intervention targeted GPs’ knowledge of diabetes care as a necessary but not sufficient factor for practice change. Because multimedia education is more effective than a single medium [18], the ALM included a range of features and presentation types including: evidence-based Australian clinical guidelines, video demonstrations, case studies, knowledge-based quizzes, clinical audit, self-reflection activities, and a moderated peer discussion forum. The ALM comprised approximately six hours of learning activity, for which GPs received CPD points via their professional body. Content for the ALM was developed in consultation with rural GPs and diabetes specialists to ensure accuracy and relevance to the rural GP population. The online ALM was trialled by a small sample of GPs and diabetes specialists to ensure that the final program was user-friendly, accurate, and relevant to GPs.

2. Access to specialist advice: Because rural GPs may not have access to a diabetes specialist in their town, every mailing to promote the ALM also promoted the availability of an on-line request form for specialist advice regarding diabetes, accessed by secure log in. A diabetes specialist was assigned to manage queries from GPs in the intervention towns. This enabled GPs to access advice on applying the diabetes management principles learned in the educational program in their day-to-day practice, and to ask for advice on more complex cases that arose. Importantly, this represents a mechanism for case-based learning, which has been demonstrated to be one of the most promising forms of CME [18].

3. Provision of town-based performance feedback: GPs were provided with town-based feedback which contained de-identified information about the proportion of diabetic patients in the town receiving testing at the recommended frequency and within target guidelines for HbA1c and blood lipids. Systematic reviews show that audit and feedback can have modest effects on changing provider practice [24].

4. Provision of comparative feedback: GPs were provided with a summary of the range of performance per GP in their town. This takes the form of a graph showing the proportion of patients per GP who meet guidelines for test frequency and management (meeting HbA1c targets). Comparative feedback has been shown to be an effective means of changing surgeons’ behavior [33,34]. Both forms of feedback were derived from de-identified data provided by local pathology laboratories.

##### Control group

No interventions by the research team are being provided to this group. There ae no restrictions on GPs’ access to other available forms of diabetes information and education opportunities during the period of the study.

##### Sample size

Assuming that 50% of subjects will be controlled in the usual-care group (*i.e.*, have a HbA1c level below 7%) and that an absolute increase of 10% is important (*i.e.*, an increase to 60% in the intervention group) then, assuming no cluster effect, the study would require 408 subjects per treatment arm to have 80% power of detecting a 10% difference at the 5% significance level. However with 14 clusters, an average of 464 diabetic patients within each cluster and an estimated intraclass correlation associated with the outcome of 0.015, the design effect of this study will be 7.9, and therefore a total of 6,490 subjects will be required. Assuming each of the 14 towns has an average of 20,000 persons and an average rate of being treated for diabetes of 2.9%, there would a total of 8,120 subjects with diabetes in the study.

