Towns were matched in pairs within each state on the above variables, proportion of population identified as Indigenous, and socio-economic status (SES). Indigenous population was incorporated in the matching process because the prevalence of diabetes is higher among Indigenous Australians than in the general population [26]. SES using the Socio-Economic Index for Areas (SEIFA) was also included in the matching process because diabetes was two to two-and-a-half times more prevalent among those in the lowest versus the highest socioeconomic group [26]. The town matching process was as follows: Towns were sorted by total population, and pairs selected within each state which were the most similar; priority was given to average ARIA+, then total population, followed by Indigenous population (although for instances of a large difference in indigenous population between two towns, general population was of less importance), and then SEIFA, because all towns had similar SEIFA codes. Once towns had been divided into pairs (NSW = 7 pairs, Queensland = 6 pairs, Victoria = 2 pairs), they were ranked according to the ‘best’ pairs. A minimum distance of 100 km between paired towns was required to prevent contamination between experimental and control communities. An initial matching process incorporating all of the above criteria for inclusion, exclusion, matching, and contamination prevention indicated that there were 17 potentially matched pairs of towns (*i.e.*, 34 towns). The pathology laboratories operating in each of the 34 towns were verified via discussion with pathology providers and searching of the electronic yellow pages to identify any towns where the two collaborating pathology laboratories provided a low proportion of the pathology services. This excluded a further six pairs of towns, leaving 11 matched pairs of towns, all of which were in NSW and Queensland. One town from each matched pair was randomly allocated to the intervention group and the other to the control group. As indicated in the sample size section, a minimum of seven matched pairs (14 towns) will be required at follow-up. Given the possibility that pathology laboratory presence in a selected town may change over the course of the study with the result that one or more towns may become ineligible, all 11 town pairs were included in the study.

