##### Statistical methods

Changes in the proportion of patients in each town exhibiting glycaemic control, appropriate frequency of testing for each of HbA1c, blood lipids, urinary albumin, and control of lipids and albumin will be assessed at baseline and post-test as described in the measures section. Analysis of the predictors of metabolic control, using age and gender will also be assessed. Analyses using cluster-level summaries are more robust than analyses based on individual-level data when there are fewer than 15 clusters per treatment arm [35]. Therefore, the primary outcome for this study will be analysed by calculating the proportion of subjects with a HbA1c level below 7% within each cluster and then comparing the proportion of the intervention group with the proportion of the control group using a two sample t-test. The main analysis will be conducted with all the available data using the intention-to-treat principle. Subgroup analyses will be conducted by gender and age group. A similar approach will be used to test the secondary outcomes.

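### At the seven-pair minimum, the planned t-test on town proportions has about 76% power, not the 80% used to size the trial

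*Protocol article*

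**What the plan says.** All references are to the protocol article.

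- **Sample size, individual level.** The section starts from "Assuming that 50% of subjects will be controlled in the usual-care group" and "an increase to 60% in the intervention group", and states that without clustering "the study would require 408 subjects per treatment arm to have 80% power of detecting a 10% difference at the 5% significance level".
- **Sample size, clustering.** "with 14 clusters, an average of 464 diabetic patients within each cluster" and an intraclass correlation of 0.015, it finds that "the design effect of this study will be 7.9, and therefore a total of 6,490 subjects will be required".
- **Sample size, availability.** From 20,000 persons per town and a treated-diabetes rate of 2.9%, it expects that "there would a total of 8,120 subjects with diabetes in the study".
- **Selection and matching of town sample.** Citing the sample size section, it says that "a minimum of seven matched pairs (14 towns) will be required at follow-up". All 11 matched pairs were kept because some towns might become ineligible.
- **Statistical methods.** The primary outcome is reduced to one proportion per town, and the arms are compared "using a two sample t-test". The reason given for cluster-level summaries is that there are fewer than 15 clusters per arm. All available data are to be used.

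**The concern.** The sample size and the analysis rest on different tests. A design effect corrects the variance for clustering, but it leaves the normal critical value of 1.96 in place. A t-test on seven plus seven town proportions has 12 degrees of freedom and a critical value of 2.18. The Statistical methods section recognises that few clusters matter for the choice of analysis, but the Sample size section makes no allowance for it.

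At stake is the seven-pair minimum, which is how the protocol expresses the number of towns it can afford to lose. If seven pairs do not deliver 80% power under the planned test, that minimum is set too low for its stated purpose. The figure of 8,120 beside a requirement of 6,490 may also reassure a reader that there is slack, when patients are not the limiting quantity.

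**Working it through.** **Inputs (Sample size section unless noted).** Proportions 0.50 and 0.60; 5% significance; 80% power; intraclass correlation 0.015; 14 towns, so 7 per arm; 464 patients per town in the design effect; 20,000 × 2.9% = 580 expected per town. Two-sample t-test on town proportions (Statistical methods). Minimum of 7 pairs and 11 pairs randomised (Selection and matching of town sample). Sidedness is not stated, but 408 reproduces only with a two-sided test; a one-sided test would give about 305, or about 325 with continuity correction.

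**Step 1: the plan's own figures.**
- Two proportions, two-sided 5%, 80% power: 388 per arm, or 408 with continuity correction. The stated 408 is reproduced.
- Design effect = 1 + (464 − 1) × 0.015 = 7.945, stated as 7.9.
- Total = 2 × 408 × 7.945 = 6,483 (6,487 with 7.95), against the stated 6,490.
- Available = 14 × 580 = 8,120, as stated.

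**Step 2: power of the planned test at seven towns per arm.** With k towns per arm, m patients per town and design effect DE:

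SE = √[(0.25 + 0.24) × DE / (k × m)], non-centrality = 0.10 / SE, degrees of freedom = 2k − 2, with power from the noncentral t distribution.

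- m = 464: DE = 7.945; SE = √(0.49 × 7.945 / 3,248) = 0.0346; non-centrality 2.888; critical value 2.179; power **75.5%**.
- m = 580: DE = 1 + 579 × 0.015 = 9.685; SE = √(0.49 × 9.685 / 4,060) = 0.0342; non-centrality 2.925; power **76.6%**.

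Beta-binomial simulation of the t-test (40,000 replicates) gives 75.5% and 76.1%. With the same standard errors and a critical value of 1.96, power would be 82.3% and 83.3%. The loss therefore comes from the degrees of freedom.

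**Step 3: do the extra patients help?** The effective total is 14 × 464 / 7.945 = 818 at 464 per town and 14 × 580 / 9.685 = 838 at 580. The additional 8,120 − 6,490 = 1,630 subjects add about 20 effective subjects and 1 point of power. With unlimited patients per town, DE/m tends to 0.015, SE = √(0.49 × 0.015 / 7) = 0.0324, and power reaches only 80.8%.

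**Step 4: more towns.**

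| Pairs | df | Power, 464 per town | Power, 580 per town |
|---|---|---|---|
| 7 | 12 | 75.5% | 76.6% |
| 8 | 14 | 81.9% | 82.8% |
| 11 | 20 | 93.1% | 93.6% |

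**The case against.** **The trial as randomised has ample power.** This stands. Eleven pairs were kept precisely as a reserve, and they give 93 to 94%. The shortfall arises only if four pairs are lost, and it is then about 4 points. The protocol also attaches no action to reaching seven pairs. A reader might infer that the trial is underpowered; the documents do not support that.

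**The design effect belongs to the wrong town size.** A reader might infer that 7.9 and 6,490 are errors, because the same paragraph expects 580 patients per town, and that they should become 9.7 and 2 × 408 × 9.685 = 7,903. This does not hold. With 14 towns fixed, 6,490 is close to 14 × 464 = 6,496, so 464 can be read as the number required per town and 580 as the number expected. The replacement would not agree with itself: 7,903 / 14 is about 565 per town, not 580. Solving 7m = 408 × [1 + (m − 1) × 0.015] gives m of about 457, or about 6,394 in total, near the published figure. Nor does the protocol claim that the excess over 6,490 compensates for anything.

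**A paired analysis would do worse.** With seven pairs and no gain from matching, a paired t-test would have 67 to 69% power. The protocol does not plan that test, so the figure does not measure this shortfall.

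**Uncertainty in the intraclass correlation is larger.** This is true. At seven towns per arm, power is 88 to 89% at 0.010 and about 65% at 0.020, and 80% is reached at about 0.013 to 0.014. That argues for modest language, but 0.015 is the protocol's own value, and its 80% should hold at that value for the test it plans.

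**Conclusion.** The concern holds for the power claim at the minimum number of towns. Under the planned two-sample t-test, seven pairs give about 76% power (75.5 to 76.6%), roughly 4 points short of 80%. The expected 8,120 subjects do not make up the difference; only more towns can.

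The figures assume 50% against 60%, an intraclass correlation of 0.015, equal town sizes and no variance reduction from matching or baseline adjustment. Unequal town sizes would lower power, and eligible populations run from 10,000 to 30,000. Effective matching or adjustment could raise it, but the protocol gives no figure for either.

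The fault lies in the reference distribution used for sizing, not in the arithmetic. It matters only if follow-up falls to seven pairs.

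**What to change.** 1. In Sample size, restate power for the planned cluster-level t-test: about 76% with seven pairs, 82 to 83% with eight and 93 to 94% with all 11, and give the assumptions.
2. In Selection and matching of town sample, either set the minimum at follow-up to eight pairs (16 towns), or keep seven and state that power there is about 76%.
3. Keep 7.9 and 6,490. Add one sentence saying that 464 is the required and 580 the expected number of patients per town, and that the excess adds only about 1 point of power.

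The cost is rewording. Eleven pairs are already randomised, so no towns, patients or analyses are added.

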##### Statistical methods

Changes in the proportion of patients in each town exhibiting glycaemic control, appropriate frequency of testing for each of HbA1c, blood lipids, urinary albumin, and control of lipids and albumin will be assessed at baseline and post-test as described in the measures section. Analysis of the predictors of metabolic control, using age and gender will also be assessed. Analyses using cluster-level summaries are more robust than analyses based on individual-level data when there are fewer than 15 clusters per treatment arm [35]. Therefore, the primary outcome for this study will be analysed by calculating the proportion of subjects with a HbA1c level below 7% within each cluster and then comparing the proportion of the intervention group with the proportion of the control group using a two sample t-test. The main analysis will be conducted with all the available data using the intention-to-treat principle. Subgroup analyses will be conducted by gender and age group. A similar approach will be used to test the secondary outcomes.

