#### Primary aim

To test whether a rural GP-focused intervention involving Continuing Medical Education (CME), reminders and feedback can improve clinical outcomes as measured by glycaemic control.

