### Measures

#### Primary outcome

##### Glycaemic control

The incidence and progression of complications of diabetes are reduced for people with lower HbA1c [8-10]. Therefore, guidelines recommend an overall target of ≤7.0% for HbA1c [6]. Using the most recent HbA1c for each case within each 24-month timeframe, the mean HbA1c across the town, and the proportion of all cases whose most recent HbA1c value is ≤7.0%, was determined.

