### Standard population guidelines may not be appropriate for all cases

Higher cut-off points for glycaemic control (*e.g.*, 8% for HbA1c in older patients) may be recommended in some cases. The primary outcome analysis relates to changes in mean HcA1c levels and would, therefore, be relatively unaffected by this factor. Analyses relating to the proportion of cases in each town achieving glycaemic control may require analyses to apply varying cut points with respect to age, however this does introduce an additional element of arbitrariness with respect to which age cut-offs are used.

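### The article gives conflicting statements of the primary outcome: the town proportion with HbA1c below 7% is sized and tested, but the discussion says the primary analysis is on mean HbA1c and defends the trial on that basis

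*Protocol article*

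**What the plan says.** Five places in the protocol article bear on which measure is primary.

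- **Primary aim.** The intervention is to be tested on whether it "can improve clinical outcomes as measured by glycaemic control". This does not choose a measure.
- **Measures, Primary outcome, Glycaemic control.** From each case's latest HbA1c in each 24-month window, "the mean HbA1c across the town, and the proportion of all cases whose most recent HbA1c value is ≤7.0%, was determined". Both measures stand under the primary heading, with no order between them.
- **Sample size.** The calculation concerns the proportion controlled, 50% against 60%, with control described as HbA1c below 7%.
- **Statistical methods.** "the primary outcome for this study will be analysed by calculating the proportion of subjects with a HbA1c level below 7% within each cluster", followed by "comparing the proportion of the intervention group with the proportion of the control group using a two sample t-test".
- **Discussion, Standard population guidelines may not be appropriate for all cases.** After noting that higher cut-offs may be advised for some patients, such as older ones: "The primary outcome analysis relates to changes in mean HcA1c levels and would, therefore, be relatively unaffected by this factor". The next sentence treats the proportion as something separate: "Analyses relating to the proportion of cases in each town achieving glycaemic control may require analyses to apply varying cut points with respect to age". It adds that choosing age cut-offs is somewhat arbitrary.

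**The concern.** Statistical methods and the discussion cannot both be right about the primary analysis. The discussion sentence is hard to read as loose wording for the proportion, because the sentence after it sets the proportion analyses apart. The article does not declare co-primary outcomes, a testing order or an adjustment for two tests.

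Two things are at stake. First, the discussion uses the supposed mean-based primary analysis to answer a real validity question, namely that a single cut-off may not suit every patient. If the proportion is primary, that answer is lost, because a proportion at a fixed threshold is the measure most exposed to the problem. Second, a later report could cite one section or another to present either measure as the pre-specified primary outcome. The 5% error rate would then not hold, and the sample-size statement would cover only one of the two.

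**Working it through.** **1. Which measure does the sample size support?**

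Inputs from Sample size: 50% and 60% controlled, 80% power, 5% level (two-sided reproduces the stated figure), 14 towns, 464 patients per town, intraclass correlation 0.015.

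- Unclustered size per arm: [1.960·√(2·0.55·0.45) + 0.842·√(0.5·0.5 + 0.6·0.4)]² / 0.10² gives 388 rounded up. With the continuity correction it is 408, the stated figure.
- Design effect: 1 + (464 − 1)·0.015 = 7.945 (stated 7.9).
- Total: 2·408·7.945 = 6,483 (stated 6,490; 14·464 = 6,496).

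The stated size reproduces, and it is for the proportion.

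**2. Is there a basis for power on the mean?**

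The article gives no standard deviation, target difference or intraclass correlation for mean HbA1c, so no power can be derived. As an illustration only, assume the same intraclass correlation of 0.015 and a standard deviation of 1.0 to 2.0 HbA1c points.

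- Effective size per arm: 7·464 / 7.945 = 408.8.
- Detectable difference: SD·√(2/408.8)·(1.960 + 0.842) = 0.196·SD, or about 0.20 to 0.39 points (normal approximation).

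**3. How correlated are the two town-level measures?**

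The article gives no correlation. Both measures come from the same latest HbA1c values in the same towns, so it should be high. Assume normal values scaled to SD 1, 50% at target, and towns that differ only by a shift in location.

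- Between-town variance of the proportion: 0.015·0.25 = 0.00375, SD 0.0612.
- Implied SD of the shift: 0.0612 / 0.399 = 0.153 (0.399 is the normal density at its centre).
- Variance of the town mean: 0.153² + 1/464 = 0.0257.
- Variance of the town proportion: 0.00375 + 0.25·0.985/464 = 0.00428.
- Covariance in absolute value: 0.153·0.0612 + 0.399/464 = 0.0103.
- Correlation in absolute value: 0.0103 / √(0.0257·0.00428), about 0.98.

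With no between-town variation it falls to 0.399/0.5 = 0.80.

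**4. False-positive chance if either test may carry the claim**

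Two-sided 5% t-tests on town summaries, 7 towns per arm, simulated under no effect:

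| Assumed correlation | Chance that at least one is significant |
|---|---|
| 0 (upper limit: 1 − 0.95²) | 9.75% |
| 0.5 | 9.3% |
| 0.7 | 8.5% |
| 0.8 | 8.0% |
| 0.9 | 7.2% |
| 0.95 | 6.6% |
| 0.98 | 6.1% |

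With 11 towns per arm, the results for correlations from 0 to 0.95 are nearly the same. Over the range supported in step 3 (0.8 to 0.98), the error is about 6% to 8%.

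**5. Is the proportion itself defined once?**

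No. The Measures section counts a case as controlled at ≤7.0%; Sample size and Statistical methods count it below 7%. A case at exactly 7.0% is controlled under one definition and not under the other.

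**The case against.** The strongest reply is that the operative sections already agree. Statistical methods names the measure, the unit and the test, and Sample size uses the same proportion. The competing statement is one sentence in a limitations section, with no test, effect size or power for the mean. The Measures section reports what is computed for glycaemic control and does not call the two measures co-primary. The full protocol or analysis plan, which is not shown, may simply follow Statistical methods.

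Much of this stands. A reader might infer that the plan offers two fully specified tests that can equally be claimed as primary. The article does not support that, since only the proportion has a test and a size. Error inflation would arise only if the choice were in fact made after the results were seen.

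A reader might also put the inflation at 9% or more by assuming a correlation of 0.5 or lower. That is hard to defend when both measures come from the same HbA1c values. Nor does the article support adding a further amount for age-varying cut-points. It says only that these may be needed, warns that they are arbitrary, and fixes 7% for the primary test; nothing says they would replace it.

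The reply does not remove the conflict. Silence on the primary analysis could be left to an analysis plan, but here the article states it twice and differently, so one published statement is wrong whatever that plan says.

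**Conclusion.** The conflict is real and the article does not resolve it. The balance of the text points to the proportion as the intended primary outcome. On that reading, the discussion's statement about the mean is wrong, its reassurance about cut-offs does not apply to the sized and tested outcome, and the Primary outcome section is ambiguous. These conclusions need no assumption about correlation.

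The error-rate consequence is conditional and modest: about 6% to 8% in place of 5% if either measure could be reported as primary. It rests on an assumed correlation of 0.8 to 0.98, itself based on towns differing by a location shift. If towns also differ in the shape of the HbA1c distribution, the correlation could be lower and the error higher, up to the limit of 9.75%.

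**What to change.** Make these changes before post-test data are extracted:

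- **Measures, Primary outcome.** Name the town proportion of cases whose most recent HbA1c is at target as the single primary outcome, and move mean HbA1c to the secondary outcomes.
- **Threshold.** Use one definition in Measures, Sample size and Statistical methods, reconciling ≤7.0% with below 7%.
- **Discussion, Standard population guidelines.** Remove the statements that the primary analysis is on the mean and that it is relatively unaffected by the cut-off. Acknowledge that the primary outcome depends on a fixed threshold.
- **Age-varying cut-points.** Confine any such analysis to a sensitivity analysis, with its cut-points specified in advance.

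The cost is wording only. The stated sample size and primary test stay as they are, and the primary test keeps the full 5% level. Timing allows it: Trial status reports baseline complete and the intervention nearing its end, and post-test measures cover the 24 months after the intervention stops.

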### Data extraction procedure

For each case the following de-identified unit record data were extracted from pathology laboratory records: date of birth, gender, de-identified doctor code, postcode of doctor’s clinic, postcode of patient, date and value of each HbA1c test, date and value of each cholesterol test, date and value of each triglycerides test, date of each HDL cholesterol test, date and value of each LDL cholesterol test, and date of each urinary albumin test. The unit record data were extracted for three time periods: pre-test measures were taken over the 24 months prior to the intervention retrospectively; during the intervention, measures were collected prospectively; post-test measures will be taken in the 24 months following the termination of the intervention. Where both pathology companies operate in the same town, the two separate data sets will be combined to produce a single data set for each town.

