##### Trial status

The study has ethical approval from the Human Research Ethics Committees of Monash University and the University of Newcastle. The trial has been registered as a trial at the Australian New Zealand Clinical Trials Registry (ANZCTR) registration number ACTRN 12611000553976 at http://www.ANZCTR.org.au/ACTRN12611000553976.aspx. To date, the baseline measurement phase of the trial has been completed and the intervention phase is nearing completion.

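### The named primary t-test has no baseline term although the 24-month baseline is held; the text elsewhere speaks of change, and the choice affects precision, not validity

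*Protocol article*

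**What the plan says.** The Statistical methods section of the protocol article describes the primary analysis as "calculating the proportion of subjects with a HbA1c level below 7% within each cluster and then comparing the proportion of the intervention group". The comparator is the control arm, and the method named is an unpaired t-test on the town values. That sentence has no baseline covariate, change score or pair term. Secondary outcomes are to be handled in a similar way.

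The same section opens differently: "Changes in the proportion of patients in each town exhibiting glycaemic control", along with the testing-frequency and lipid and albumin measures, "will be assessed at baseline and post-test as described in the measures section". No test or model is attached to that statement. In the Discussion, under the heading on standard population guidelines, the article says "The primary outcome analysis relates to changes in mean HcA1c levels", which is both a change and a different summary (mean, not proportion).

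The baseline exists. Under Data extraction procedure, "pre-test measures were taken over the 24 months prior to the intervention retrospectively" and "post-test measures will be taken in the 24 months following the termination of the intervention". Under Primary outcome, the glycaemic measure is computed from each case's latest HbA1c in each 24-month window. Under Trial status, "the baseline measurement phase of the trial has been completed".

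**The concern.** There are two linked problems. First, the article supports at least two primary analyses, one on post-test values only and one on change from baseline, and these can give different answers on the same data.

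Second, if the named test is taken literally, a covariate already in hand goes unused. Towns were matched on remoteness, population, Indigenous share and socio-economic status, not on baseline glycaemic control. With 7 to 11 towns per arm, persistent differences between towns stay in the error of the comparison. Under the plan's ICC most of the variance of a town proportion lies between towns, so more patients per town would hardly reduce it. Baseline adjustment can, to the extent that those differences persist.

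**Working it through.** **Inputs.** From Sample size: 50% against 60% controlled, 5% level, 80% power, 408 per arm before clustering, 14 towns, m = 464 per town, ICC 0.015. From Selection and matching of town sample: 11 pairs enrolled, seven needed at follow-up. The town-level correlation r between baseline and post-test proportions is not given. It is an assumption, shown from 0 to 0.7.

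**1. The plan's own figure.** A two-sided 5% test with continuity correction gives 408 per arm (388 without). Design effect = 1 + 463 × 0.015 = 7.945. Total = 2 × 408 × 7.945 = 6,483, against 6,490 stated. It reproduces and is not in dispute.

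**2. Variance of a town proportion**, p(1−p) × 7.945/464:
- p = 0.5: 0.25 × 7.945/464 = 0.00428
- p = 0.6: 0.24 × 7.945/464 = 0.00411
- average 0.004195, an SD of about 6.5 points
- between-town share: 0.015 × 464/7.945 = 88%

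**3. The named test.** SE = √(2 × 0.004195/k), with noncentral-t power on 2k−2 df.
- k = 7: SE 3.46 points, power 75.5%. The normal approximation gives 82.3%, so the shortfall from 80% comes from using t on 12 df.
- k = 11: SE 2.76 points, power 93.1%.

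The same SEs describe a chance baseline difference between arms. It would exceed 5 points, half the target effect, about 15% of the time with 7 towns per arm and 7% with 11.

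**4. With baseline.** ANCOVA: variance × (1−r²), 2k−3 df. Change score: variance × 2(1−r), 2k−2 df.

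| r | ANCOVA, 7 per arm | Change score, 7 per arm | ANCOVA, 11 per arm | Change score, 11 per arm |
|---|---|---|---|---|
| 0 | 74.9% | 46.8% | 93.0% | 68.3% |
| 0.3 | 78.7% | 61.2% | 94.9% | 82.9% |
| 0.5 | 85.8% | 75.5% | 97.7% | 93.1% |
| 0.7 | 95.7% | 92.7% | 99.8% | 99.3% |
| unadjusted | 75.5% | | 93.1% | |

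The change score matches the unadjusted test at r = 0.5 and is worse below it, because 2(1−r) exceeds 1 there.

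**5. A refinement.** The factor 1−r² treats the baseline slope as known. Estimating it inflates the variance on average by 1 + 1/(2k−4) for a normal covariate: 1 + 1/10 = 1.10 at k = 7 and 1 + 1/18 = 1.06 at k = 11. Averaging power over that inflation, and checking by simulation, gives about 71%, 75%, 83% and 94% at r = 0, 0.3, 0.5 and 0.7 with 7 towns per arm, and 92%, 94%, 97% and 99.6% with 11. Setting (1−r²) × 1.10 = 1 gives a break-even variance at r = √(1 − 1/1.10) = 0.30 with 7 per arm. With 11 it is √(1 − 1/1.056) = 0.23.

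**6. A fully paired regression.** Regressing within-pair post-test differences on within-pair baseline differences leaves pairs − 2 df, so 5 with seven pairs. Using variance × (1−r²), 5 df and no gain from matching (an assumption), power is about 68% at r = 0.3 and 76% at r = 0.5, against 75.5% for the unadjusted test. With 580 per town (20,000 × 2.9%) these are 69% and 77%, against 76.6%.

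**The case against.** Four points can be made for the plan.

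The named test is valid. Over randomisation the unadjusted comparison of town proportions is unbiased, and its standard error already contains between-town variation. A reader might infer that chance baseline imbalance biases the trial or invalidates its interval. The documents do not support that. This stands in full: the issue is efficiency.

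The article does mention change, in two places. A reader might infer from the t-test sentence that baseline is simply ignored. That is also too strong, since a change analysis may be intended and the full analysis plan, not shown, may give the covariates. It does not remove the point, however. The article does not leave the primary test open: it names one without baseline, and its statements about change fit neither that test nor each other on the summary used.

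The gain may be small. All 11 pairs were enrolled, and at the plan's own 10-point effect the unadjusted test then has 93.1% power. The gain matters mainly if towns drop out, which the article anticipates, or if the true effect is smaller. This stands.

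A high r cannot be presumed. A two-year intervention separates the windows, individuals enter and leave the data, and the article foresees changes in HbA1c equipment and methods. An assay change between windows would weaken baseline as a proxy for a stable town difference. This stands, and is why the range must include low r.

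**Conclusion.** The point holds as one of inconsistency and lost precision. The primary test as named uses no baseline although the measure is held, and two other statements imply that baseline enters. With 7 towns per arm, ANCOVA moves power from 75.5% to between about 75% (r = 0) and 96% (r = 0.7); allowing for the estimated slope, to between about 71% and 94%. At that minimum size the gain is real only if r is clearly above 0.3. With 11 towns per arm there is little to win at a 10-point effect.

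These sizes rest on the plan's ICC, equal town sizes of 464, normal-theory power for town proportions, and an assumed r. The inconsistency rests on no assumption.

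**What to change.** Bring the opening sentence of Statistical methods and the Discussion statement on mean HbA1c into line with the named test, so that one summary and one use of baseline are stated for the primary outcome.

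Before post-test data are analysed, prespecify as primary a town-level ANCOVA of the post-test proportion on arm and the town's baseline proportion, and report the unadjusted comparison as supportive. Do not substitute simple change scores, which are less precise than the unadjusted test when r is below 0.5. Do not offer the fully paired regression as an equivalent option: it leaves 5 df with seven pairs and can lose power if matching explains little.

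The cost is wording and one degree of freedom, plus the small variance from estimating the slope (step 5 of the working). Together these come to about 4 points of power with 7 towns per arm if r were zero (75.5% to about 71%). No new data are needed.
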